### Safety assessment

2.10

Safety will be evaluated according to the incidence of adverse events and the results of clinical laboratory examinations. All adverse events will be recorded. The possible association between adverse events and the intervention will be determined according to a 5-level classification: affirmative, probable, possible, suspicious, and impossible.

Any adverse events during the trial will be recorded using the “adverse event form” and continue to be investigated. Researchers will record the treatment process if needed and results until the laboratory examination results return to normal and symptoms and signs disappear. All SAEs will be reported to the research ethics committee within 24 hours. When participants become unsuitable to continue the trial due to adverse events, they will be withdrawn from the trial immediately.

Clinical laboratory examinations will include routine blood, urine, stool + occult blood, liver function, kidney function, coagulation function, glucose and D-dimer tests, and electrocardiography.

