### Sample size

2.12

The sample size was calculated by PASS software version 15 (Kaysville, UT). In a previous study, the rate of unfavorable disability (according to the mRS score) in the control group was 56%.^[15]^ We assume that the rate of unfavorable disability (according to the mRS score) in the treatment group will be 36%, that is, decreased by 20%. After a 2-sided Z test, PASS software calculated that the sample size of each group should be 129. Considering a 20% dropout rate, 312 patients will need to be enrolled.

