### Statistical analysis

2.13

Inferential statistical analyses as specified will be conducted, and all comparisons will be between the ABRS granule group and the placebo group. The statistical analyst will be blinded to the participants’ personal information and group assignment during the trial. The primary analysis will be based on the full dataset following the intention-to-treat analysis principle for all efficacy outcomes, while the secondary analysis will be based on the per protocol dataset. For the analysis of safety outcomes, a safety dataset will be used. The primary outcome will be determined by a comparison of the changes in the patients’ mRS scores between the 2 groups at 6 months after onset. The secondary outcomes will include the mortality rate, hematoma enlargement percentage, all-cause mortality rate, adverse events, TCM stroke syndrome evaluation scale score, BI, and NIHSS score. The hematoma enlargement percentage will be measured at baseline, 24, 48, and 72 hours after taking the medicine and 14 days after onset. The mortality rate, all-cause mortality rate, BI, and TCM stroke syndrome evaluation scale score will be measured at 14 days, 3 months, and 6 months after onset. The NIHSS score will be measured at 14 days after onset. The mRS score will be measured at 3 and 6 months after onset.

Missing data regarding the primary and secondary outcomes will be imputed using the last observation carried forward (LOCF) method. Independent *t* tests or Wilcoxon rank-sum tests will be used to analyze continuous outcomes. Chi-squared tests will be used to analyze categorical data. Analysis of variance or a generalized linear mixed model will be used for repeated measurement data. Regarding mortality, survival probabilities will be estimated using the Kaplan–Meier method. Two-sided 95% confidence intervals will be constructed for assessment, and a 2-sided alpha level of 0.05 will be used to indicate significance. Adjustments will be made for baseline imbalances. Descriptive statistics, including the number and percentage for categorical variables and the number, mean, standard deviation, median, minimum and maximum for continuous variables, will be provided. Listings of individual patient data will also be produced. A comprehensive statistical plan will be prepared and finalized prior to unblinding and analysis of the data.

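### The LOCF rule does not exempt mortality, so read literally it counts patients lost to follow-up as alive and does not fit the Kaplan-Meier analysis in the same paragraph

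*Protocol article*

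**What the plan says.** All the analysis rules at issue stand in section 2.13 (Statistical analysis) of the protocol article.

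- **Outcomes.** "The secondary outcomes will include the mortality rate, hematoma enlargement percentage, all-cause mortality rate", followed by the remaining secondary outcomes. Both mortality rates "will be measured at 14 days, 3 months, and 6 months after onset". Table 1 schedules mortality at the same three visits and has no mortality entry at enrollment.
- **Missing data.** "Missing data regarding the primary and secondary outcomes will be imputed using the last observation carried forward (LOCF) method". No outcome is exempted.
- **Methods.** "Chi-squared tests will be used to analyze categorical data", and, for deaths, "Regarding mortality, survival probabilities will be estimated using the Kaplan–Meier method". Nothing says how a patient of unknown vital status enters either analysis.

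Two other sections bear on how much may be missing. Section 2.12 (Sample size): "Considering a 20% dropout rate, 312 patients will need to be enrolled". Section 2.10 (Safety assessment) says of participants whom adverse events make unsuitable to continue that "they will be withdrawn from the trial immediately".

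**The concern.** A patient whose vital status is missing at a visit was alive when last seen, so LOCF can carry forward only one value: alive. For most outcomes the direction of LOCF error is uncertain. Here it is fixed, because every death after loss to follow-up is recorded as a survival.

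Kaplan-Meier treats the same patient differently. It removes the patient from the risk set at last contact and makes no claim about later status. The two rules can therefore give two mortality figures from one dataset, and the text does not say which stands.

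What is at stake is the reading of mortality as a safety result. If one arm loses more patients than the other, LOCF lowers its death rate more, and the arm with the poorer follow-up looks safer.

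**Working it through.** **The plan's own figures.** The article gives no mortality rate for this trial, so there is no mortality figure to reproduce. Its one computed figure, 129 per group, can be reproduced from 56% vs 36% with a two-sided 5% pooled Z test if power is 90% (power is not stated):

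[1.96·√(2·0.46·0.54) + 1.2816·√(0.56·0.44 + 0.36·0.64)]² / 0.20² = 128.4, rounded up to 129.

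That figure does not bear on this point. Only the total of 312 and the 20% dropout allowance are used below.

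**Step 1: how the rules interact.** If LOCF is applied first, every lost patient is alive at 6 months and nobody is censored before then. Kaplan-Meier with no censoring equals the crude proportion, so it would return the LOCF figure. If Kaplan-Meier is applied to the unimputed data, lost patients are censored and the estimate is unbiased when loss is unrelated to risk of death. The order decides the result, and the order is not stated.

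**Step 2: size of the understatement.** Let S14, S3 and S6 be the true proportions alive at 14 days, 3 months and 6 months. Let a fraction d of those alive be lost just after a visit, unrelated to risk of death. The deaths that LOCF misses are those among the lost between that visit and 6 months:

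- loss after the 14-day visit: S14 · d · (1 − S6/S14) = d · (S14 − S6)
- loss after the 3-month visit: d · (S3 − S6)

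The survival patterns below are assumptions, and d = 0.20 borrows the dropout allowance.

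| Assumed S14 / S3 / S6 | True 6-month mortality | LOCF, loss after 14 days | Shortfall | LOCF, loss after 3 months | Shortfall |
|---|---|---|---|---|---|
| 95 / 90 / 87% | 13.0% | 11.4% | 0.20 × 8 = 1.6 points | 12.4% | 0.20 × 3 = 0.6 point |
| 90 / 82 / 78% | 22.0% | 19.6% | 0.20 × 12 = 2.4 points | 21.2% | 0.20 × 4 = 0.8 point |
| 80 / 65 / 60% | 40.0% | 36.0% | 0.20 × 20 = 4.0 points | 39.0% | 0.20 × 5 = 1.0 point |

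In patients, 0.016 × 312 = 5.0 and 0.040 × 312 = 12.5. That is about 5 to 12 uncounted deaths in the whole trial, both arms together, when loss follows the 14-day visit.

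**Step 3: unequal loss.** Take equal true mortality in both arms, with 10% lost in one and 30% in the other, just after the 14-day visit:

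- true 22%: 22 − 0.10 × 12 = 20.8% vs 22 − 0.30 × 12 = 18.4%, a false difference of 2.4 points
- true 40%: 40 − 0.10 × 20 = 38% vs 40 − 0.30 × 20 = 34%, a false difference of 4 points

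The direction, favoring the arm with more loss, follows from the rule. The sizes follow from the assumptions.

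**The case against.** The best defense is that section 2.13 gives a general missing-data rule and then methods by type of outcome, and that the sentence on mortality, being specific, overrides LOCF. Kaplan-Meier handles loss by censoring, and mortality at the three visits can be read off the curve. This reading is plausible, and it is why calling the text an outright contradiction would go too far. But the sentence names an estimator, not a missing-data rule, and the fixed-visit mortality rates remain listed outcomes. Nothing rules out LOCF followed by a chi-squared test, though the chi-squared sentence does not mention mortality either.

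A second defense is that the promised statistical plan will settle censoring. Censoring details and the choice of test can properly wait for it. The LOCF rule, however, is already stated here without exception.

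A reader might infer more than the documents support:

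- **A larger bias.** Multiplying the whole 20% by full 6-month mortality would turn a true 20% into 16%. That needs every dropout to leave at randomization with status unknown. The 20% is a sample-size allowance for the mRS endpoint, not a forecast of lost vital status. Table 1 has no mortality entry before day 14 to carry forward.
- **Harm hidden by adverse-event withdrawals.** Section 2.10 does withdraw some patients, but it also keeps adverse events under investigation until they resolve and sends serious ones to the ethics committee within 24 hours. Nothing in the article shows that withdrawal will differ by arm.
- **Support from the hematoma-enlargement evidence.** The Discussion ties that evidence to use within 6 hours of onset. This trial enrolls at 24 to 72 hours.

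**Conclusion.** The point holds as a defect in a stated rule. As written, LOCF covers mortality, can only understate deaths, and does not fit the Kaplan-Meier analysis beside it unless a reader supplies an exemption that the text does not give.

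The understatement is about 1.6 to 4.0 percentage points if 20% of survivors are lost after the 14-day visit, and 0.6 to 1.0 point if they are lost after the 3-month visit. These figures rest on assumed 6-month mortality of 13% to 40%, on loss unrelated to risk of death, and on unknown vital status for everyone lost. If status is obtained for nearly all patients, the effect is small. Mortality is a secondary outcome, so the primary test is not directly altered. The documents do not show that harm would in fact be masked, only that the rule permits it if loss is unequal. The change is worth making because it costs so little.

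**What to change.** In section 2.13:

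1. State that LOCF does not apply to the mortality outcomes.
2. Take 14-day, 3-month and 6-month mortality from the Kaplan-Meier estimate, with patients of unknown status censored at the last date known alive.
3. Report the number with unknown vital status in each arm.
4. Seek vital status at the existing 6-month contact for every randomized patient, including those withdrawn. Censoring is unbiased only if loss is unrelated to risk of death, so this step limits how much depends on that assumption.

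The choice of test can be left to the statistical plan. The cost is a few sentences of text and minor extra follow-up effort, with no added patients.

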## Discussion

3

Cerebral hemorrhage usually has greatly negative effects and places a large economic burden on patients and their families. In recent years, under the guidance of TCM theory, ABRS has been widely used in the treatment of cerebral hemorrhage. Several animal experiments have verified the benefits of TCM for cerebral hemorrhage. Experiments have found that TCM herbs decrease oxygen and glucose deprivation-induced Ca2+ overload and endoplasmic reticulum stress while inhibiting apoptosis by decreasing mitochondrial damage.^[16]^

Previous studies have provided some evidence about the efficacy and safety of treating cerebral hemorrhage with TCM, but most of them have been literature reviews.^[17,18]^ Some clinical trials have verified the safety of TCM in acute cerebral hemorrhage, but most of these have been retrospective studies or randomized controlled studies with a small sample.^[19,20]^ Thus, a high-quality trial of the ABRS method in acute cerebral hemorrhage is necessary.

Previous randomized controlled trials have often focused on the efficacy and safety of the ABRS method for acute cerebral hemorrhage while neglecting to explore the optimal timing of the intervention. The overall trend shows that patients with acute cerebral hemorrhage can gain more benefits from adjuvant treatment with the ABRS method than from treatment with conventional Western medicine alone. However, previous randomized controlled trials of the ABRS method applied within 6 hours showed that TCM treatment was not beneficial and increased the risk of hematoma enlargement.^[21]^ At the time of writing, there are no multicenter, large-sample, prospective, double-blind, placebo-controlled randomized controlled trials exploring the best timing of intervention with the ABRS method for acute cerebral hemorrhage. This study will fill in the gap in this area and facilitate clinical decision-making.

However, this trial will also have some limitations. To obtain a more representative patient population, we will recruit participants from 7 centers. However, the study will be carried out only in China. Therefore, whether the test results can be applied in all countries needs to be further verified.

The results of this study will be of importance for patients with cerebral hemorrhage, as they will allow us to draw conclusions on the efficacy, safety, and optimal timing of intervention with the ABRS method. This study may provide clinical evidence as a basis for the treatment of acute cerebral hemorrhage with the ABRS method and improve the prognosis and quality of life of patients with cerebral hemorrhage.

## Abbreviations

Abbreviations: ABRS = activating blood and removing stasis, BI = Barthel index, CRF = case reporting form, CT = computed tomography, mRS = modified Rankin scale, NIHSS = National Institutes of Health stroke scale, TCM = traditional Chinese medicine.
